**10.4. Serious Adverse Events (SAE)**

1. An SAE is defined as an AE that meets any of the following criteria:
   1. Death not directly caused by the underlying disease or its complications.
   2. Life-threatening or potentially fatal.
   3. Requires hospitalization or prolongs existing hospitalization (complications occurring during hospitalization are considered AEs; complications prolonging hospitalization are considered SAEs).
   4. Results in persistent or significant disability or incapacity that affects the ability to work.
   5. Causes congenital anomaly or birth defect.
   6. Considered a medically important event by the investigator.
2. Special considerations for handling SAEs:
   1. Disease progression during the study or reporting period (including symptoms and signs of progression) should not be reported as SAEs.
   2. Death, hospitalization/prolongation, or disability caused by the disease itself or its direct complications are not considered SAEs.
   3. Hospitalizations due to AEs or prolonged hospital stays caused by AEs during the study are SAEs. Any initial admission to a medical institution (even if less than 24 hours) meets the criteria. Hospitalizations unrelated to AE worsening (e.g., routine workups for persistent pre-study lab abnormalities) are not considered SAEs.

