**2.1. Primary Objective**

To evaluate the safety of inhaled extracellular vesicle therapy in patients with pulmonary fibrotic lesions as identified by high-resolution computed tomography (HRCT).

1. to monitor vital signs, clinical symptoms and signs, and the incidence of adverse events on Days 1–8, Week 4, and Week 12 after enrollment.
2. to assess changes in laboratory and clinical parameters on Day 8 and Week 12, including complete blood count, urinalysis (plus pregnancy test), blood biochemistry, electrocardiogram (ECG), peripheral oxygen saturation (SpO₂), tumor markers, levels of IL-6 and IL-10, immune cell function in peripheral blood, and lymphocyte subsets.

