**8.2. Early Study Suspension or Termination by Investigators**

The investigator should suspend or terminate the study early if any of the following conditions are met:

1. Violation of inclusion criteria or fulfillment of exclusion criteria.
2. The investigator determines that the trial should not continue due to adverse events.
3. Serious safety issues arise during the study (e.g., serious adverse reactions, severe complications, or rapid disease progression).
4. The treatment is found to be ineffective or of low efficacy during the study, lacking clinical value and potentially delaying appropriate treatment.
5. Major flaws are found in the study protocol or significant deviations occur during implementation, making evaluation unreliable.
6. Other reasons deemed necessary by the investigator to suspend or terminate treatment.

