# 10. Recording Requirements for Adverse Events and Reporting/ Management of Serious Adverse Events

**10.1. Adverse Events (AE)**

1. An AE refers to any untoward medical occurrence in a participant during the course of the study, regardless of its causal relationship with the investigational product. It includes any unfavorable or unintended sign (including abnormal laboratory findings), symptom, or disease temporarily associated with the use of the investigational product, whether or not considered related to it.
2. All AEs, regardless of their relationship to the investigational product, must be recorded in the Case Report Form (CRF), including the diagnosis, onset and duration, interventions taken, treatment interruption status, corrective measures, outcome, and other possible causes.
3. All AEs occurring during the observation period—from the date of informed consent signing to study completion—must be collected, including:
4. Exacerbation of pre-existing symptoms or diseases prior to the trial (excluding the disease intended to be treated by the investigational extracellular vesicles).
5. Increased frequency or severity of pre-existing episodic events.
6. Abnormal changes detected or diagnosed after administration of the investigational extracellular vesicles, even if such abnormalities may have existed before treatment.
7. Not all abnormal lab results or other test findings (e.g., ECG or vital signs) are reported as AEs unless associated with clinical symptoms, result in treatment changes, require medical intervention, or are deemed clinically significant by the investigator. Such findings, if considered part of a clinical diagnosis or corresponding standard medical terminology (reported as an AE), should not be listed separately as AEs but reported as the diagnosis or term (e.g., anemia).

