**10.3. Assessment of Relationship Between AE and Investigational Product**

1. Investigators should evaluate the potential association between the AE and the investigational product based on the following criteria:
   1. Time of onset and time to resolution.
   2. Grading per NCI-CTCAE v5.0 definitions.
   3. Causality categorized as: definitely related, probably related, possibly unrelated, unrelated, or indeterminate. The first three categories (definitely, probably, and indeterminate) are considered related to the investigational product and will be used for calculating incidence rates of adverse reactions, with the number of such events as numerator and the total number of participants as denominator for safety evaluation.
2. All AEs or other symptoms and signs occurring during the study must be recorded on the AE page of the CRF, regardless of their relationship to the investigational treatment.
3. Any participant who receives treatment must be evaluated for toxic reactions. The severity of any AEs should be graded according to NCI-CTCAE v5.0.

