**10.6. AE Management and Follow-up**

All equipment, reagents, and techniques used in the preparation of the aerosolized EV solution follow national preparation standards and undergo strict quality control before patient administration.

Adverse reactions to aerosolized EV treatment are rare. A small number of patients may experience mild symptoms such as flushing, rash, low-grade fever, chills, nausea, or vomiting, requiring symptomatic treatment. In rare cases, patients may develop serious symptoms such as dyspnea, hypotension, tachycardia, or severe allergic reactions, necessitating immediate medical intervention.

Potential AEs and Management:：

1. Gastrointestinal reactions: 1) Use 5-HT3 receptor antagonists, corticosteroids, NK1 receptor antagonists to prevent/treat vomiting. 2) Use antidiarrheals, mucosal protectants, and intestinal antibiotics to control symptoms, promote healing, and prevent secondary infection.
2. Cardiotoxicity: 1) Avoid fluid overload; 2) Administer diuretics if needed; 3) Closely monitor ECG before, during, and 24 hours after treatment.
3. Lack of efficacy: If nebulized EVs do not alleviate symptoms or improve lung tissue repair, this has been clearly explained in the informed consent form.
4. Fever: Administer antipyretics such as acetaminophen. If persistent, investigate bacterial infection and treat accordingly.
5. Infection prevention: All EV preparation and nebulization must follow strict protocols to reduce infection risk.
6. Pain or discomfort during nebulization: Provide symptomatic relief as needed.
7. Dyspnea or mild pneumonia post-nebulization: Though rare, active treatment under close observation will be provided.
8. Cerebral embolism: Extremely rare but should remain on the alert.

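### Section 10.4 takes events attributed to the lung disease out of the SAEs, so attribution alone can move serious respiratory events out of the SAE count and the 24-hour report

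*Protocol*

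**What the plan says.** Protocol section 2.1 makes safety the primary objective; its first item is "to monitor vital signs, clinical symptoms and signs, and the incidence of adverse events". Section 11.5 answers this with summaries of treatment-emergent AEs and SAEs.

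Section 10.4 narrows what counts as an SAE in three places:
- The death criterion is limited to "Death not directly caused by the underlying disease or its complications".
- On progression: "Disease progression during the study or reporting period (including symptoms and signs of progression) should not be reported as SAEs".
- On outcomes of the disease: "Death, hospitalization/prolongation, or disability caused by the disease itself or its direct complications are not considered SAEs".

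Section 10.1 defines an AE broadly, whatever its cause, and then lists what the collected AEs include. One listed item reads "Exacerbation of pre-existing symptoms or diseases prior to the trial (excluding the disease intended to be treated by the investigational extracellular vesicles", with the parenthesis closing there. Section 10.3 adds "All AEs or other symptoms and signs occurring during the study must be recorded on the AE page of the CRF", whether or not they are related to treatment.

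Two other sections treat respiratory worsening as a safety matter. Among its grounds for suspending or ending the study, section 8.2 has "Serious safety issues arise during the study (e.g., serious adverse reactions, severe complications, or rapid disease progression", where the parenthesis also closes. Section 10.6 lists among potential AEs "Dyspnea or mild pneumonia post-nebulization: Though rare, active treatment under close observation will be provided".

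**The concern.** The product is inhaled into fibrotic lungs. If it does serious harm, an acute respiratory deterioration is a plausible form, and at the bedside this may be hard to tell from worsening of the underlying disease. Section 10.4 makes that distinction decide whether the event is an SAE at all. The usual order is to classify an event by seriousness first and judge causality afterwards. Here a causal judgement comes first and can end the process.

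Two things are at stake: the SAE incidence, which is part of the answer to the primary objective, and the 24-hour report to the authorities in section 10.5, which is tied to SAE status. Section 10.3 cautiously counts events of indeterminate causality as related. That protects the adverse-reaction rate only for events recorded as AEs, and it does not restore SAE status to an event that 10.4 has removed.

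The protocol also does not say whether the person who attributes events knows the treatment arm. Section 4.1 says only that the trial is single-blind, and section 5.5.2 blinds staff to one another's assessments without mentioning allocation. If the arm is known, attribution could differ between arms.

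**Working it through.** The protocol gives no event rate or power basis for 12 patients per arm (section 6), so there is no plan figure to reproduce. The check is a comparison of the text, followed by arithmetic for scale.

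**1. The sections side by side**

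| Question | Points one way | Points the other way |
|---|---|---|
| Is worsening of the treated disease an AE? | Yes: general definition in 10.1; recording rule in 10.3 | Unclear: the parenthesis in one listed item of 10.1 |
| Is serious worsening attributed to the disease an SAE? | No: three statements in 10.4 | 8.2 treats rapid progression as a serious safety issue |
| Are dyspnea and pneumonia possible product reactions? | Yes: 10.6 | 10.4 removes symptoms and signs of progression, which can look the same |
| Are exacerbations and deaths collected? | Yes: 4.3.2 and Table 1 (exacerbations at every visit from D1 to D360) | Not named in 11.5; exacerbations are a secondary objective (2.2) and an efficacy endpoint (9.1) |

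The exclusion is firm for SAEs and only ambiguous for AEs. The data exist, but they sit outside the planned safety summary.

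**2. What the SAE table would show**

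Assume 2 of 12 treated patients have a serious respiratory event. Limits are exact two-sided 95%. For zero events the upper limit is 1 − 0.025^(1/12) = 0.265.

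| Attributed to the disease | SAE table | Exact 95% limits |
|---|---|---|
| none | 2/12 = 16.7% | 2.1% to 48.4% |
| one | 1/12 = 8.3% | 0.2% to 38.5% |
| both | 0/12 = 0% | 0% to 26.5% |

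Each reclassified patient moves the arm's rate by 1/12 = 8.3 percentage points.

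**3. Chance that the SAE table shows any event**

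Let p be the assumed true risk and m the assumed share attributed to the disease. The chance of at least one counted event in 12 is 1 − (1 − p(1 − m))^12. For example, with p = 0.2 and m = 0.5 it is 1 − 0.9^12 = 0.72.

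| p | m = 0 | m = 0.5 | m = 0.8 |
|---|---|---|---|
| 10% | 72% | 46% | 22% |
| 20% | 93% | 72% | 39% |
| 30% | 99% | 86% | 52% |

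**4. Would the efficacy comparison recover the signal?**

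Section 11.4 compares progression events by chi-square, or by chi-square or Fisher's exact test for individual events. With 12 per arm and none on placebo, Fisher's test needs 5 versus 0 (p = 0.037; 4 versus 0 gives p = 0.093). The uncorrected chi-square for k versus 0 is 24(12k)²/[12·12·k(24 − k)] = 24k/(24 − k). This gives 2.18 for k = 2, 3.43 for k = 3 and 4.80 for k = 4, against a critical value of 3.84. An imbalance of 2 versus 0 would not reach significance under either test, so the efficacy analysis is no substitute for a by-arm safety table.

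**The case against.** A reader might infer that the AE and SAE rules together exclude lung worsening, so that respiratory harm disappears from the trial. The documents do not support this. The parenthesis in 10.1 limits one example in an inclusive list, while the general definition there and the recording rule in 10.3 still capture symptoms and signs whatever their cause. Exacerbations are collected at every post-baseline visit, and 4.3.2 has deaths, length of stay and mechanical ventilation recorded. Vital signs, symptoms and oxygen saturation remain in the primary objective. Events can be reclassified, but they are not lost.

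A reader might also infer that attribution is unblinded. Section 5.5.1 has the principal investigator store a copy of the sealed codes, and 7.1 has investigators sign for EV product by subject. Neither settles whether the person judging events knows the arm, so this is a possibility only.

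Nor does the stopping provision in 8.2 clearly depend on the 24-hour report. It is a decision by the investigator, who can see the patients at this single center.

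Lastly, 10.4 removes only events caused by the disease. A deterioration caused by nebulization falls outside those words if it is recognised as such.

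All of this limits the scope. It does not answer the remaining point: that recognition is the difficult step, 10.4 makes SAE status depend on it, and 11.5 names no summary of deaths or exacerbations that would show the events regardless of attribution.

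**Conclusion.** The concern holds as an inconsistency in the SAE definition and a gap in the safety tabulation. Section 10.4 lets attribution to the lung disease remove a serious event from SAE incidence and from the 24-hour report. This conflicts with 8.2 and 10.6, and it sits badly with the cause-neutral AE wording in 10.1 and 10.3. For AEs, the finding goes no further than ambiguity in 10.1.

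The size depends on assumptions. The 2/12 is hypothetical, and the fall to 0/12 requires both events to be attributed to the disease. The rates and attributed shares in the probability table are also assumed. What does not depend on them is that one reclassified patient shifts an arm by 8.3 percentage points, which is large for a trial whose primary question is safety. Any difference in attribution between arms would add bias, but whether that can arise turns on blinding that the protocol leaves unstated.

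**What to change.** Reconcile sections 10.1, 10.3 and 10.4 with 8.2, 10.6 and 11.5. Specifically:

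- In 10.4, for safety analysis and reporting, apply the seriousness criteria to deaths, unplanned hospitalizations, and acute exacerbations or respiratory worsening, whatever the presumed cause. Record causality as a separate item.
- In 10.1, say plainly whether worsening of the treated disease is recorded as an AE, in line with the general definition and 10.3.
- In 11.5, name deaths, unplanned hospitalizations and acute exacerbations as events tabulated by arm, irrespective of attribution. This needs placebo patients in the Safety Analysis Set. Section 11.1 describes that set only as randomized subjects who received EVs, so its wording should be checked at the same time.
- State whether those who attribute events know the allocation.

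The separate exclusion in 10.4 of admissions unrelated to AE worsening, such as routine work-ups, can stay. Exacerbations can also remain an efficacy outcome. The cost is a change of wording and a few more SAE reports among 24 patients. No new data collection is needed for exacerbations, deaths or hospital stay, since section 4.3.2 already provides for recording them.

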**10.5. AE Documentation and Reporting**

All AEs should be reported to relevant institutional departments. If a serious, unexpected AE related to the study occurs that falls within the scope of the hospital’s clinical trial liability insurance, compensation for the patient will be sought through the insurer.

- All AEs: Interventions should be promptly taken and recorded in the CRF.
- SAEs: Immediate interventions are required. The event must be documented in the CRF and reported to the Ethics Committee, Clinical Trial Institution, and manufacturing unit. Additionally, it must be reported within 24 hours to national and provincial health authorities and the food and drug regulatory administration.

**10.6. AE Management and Follow-up**

All equipment, reagents, and techniques used in the preparation of the aerosolized EV solution follow national preparation standards and undergo strict quality control before patient administration.

Adverse reactions to aerosolized EV treatment are rare. A small number of patients may experience mild symptoms such as flushing, rash, low-grade fever, chills, nausea, or vomiting, requiring symptomatic treatment. In rare cases, patients may develop serious symptoms such as dyspnea, hypotension, tachycardia, or severe allergic reactions, necessitating immediate medical intervention.

Potential AEs and Management:：

1. Gastrointestinal reactions: 1) Use 5-HT3 receptor antagonists, corticosteroids, NK1 receptor antagonists to prevent/treat vomiting. 2) Use antidiarrheals, mucosal protectants, and intestinal antibiotics to control symptoms, promote healing, and prevent secondary infection.
2. Cardiotoxicity: 1) Avoid fluid overload; 2) Administer diuretics if needed; 3) Closely monitor ECG before, during, and 24 hours after treatment.
3. Lack of efficacy: If nebulized EVs do not alleviate symptoms or improve lung tissue repair, this has been clearly explained in the informed consent form.
4. Fever: Administer antipyretics such as acetaminophen. If persistent, investigate bacterial infection and treat accordingly.
5. Infection prevention: All EV preparation and nebulization must follow strict protocols to reduce infection risk.
6. Pain or discomfort during nebulization: Provide symptomatic relief as needed.
7. Dyspnea or mild pneumonia post-nebulization: Though rare, active treatment under close observation will be provided.
8. Cerebral embolism: Extremely rare but should remain on the alert.
9. Allergic reactions: For rash or itching: slow infusion or pause; administer 5–10 mg dexamethasone IV and/or 25–50 mg promethazine IM. If symptoms persist or worsen, discontinue nebulization and initiate anti-allergy treatment. For anaphylactic shock: stop nebulization immediately, lay the patient flat, and keep warm. Subcutaneously inject 0.5–1 ml of 0.1% epinephrine; repeat every 30 min if necessary. Administer oxygen therapy; if respiration is inhibited, use mechanical ventilation. For laryngeal edema, perform intubation or tracheotomy. Administer dexamethasone 5–10 mg IV or hydrocortisone 200 mg with 500 ml 5%/10% glucose IV. Use pressor agents like dopamine, norepinephrine, and antihistamines like methylene blue or promethazine IM. For cardiac arrest, initiate CPR and correct acidosis promptly. Closely monitor and document vital signs, urine output, and clinical changes. Patients in critical condition should not be moved.
10. Chills: Administer 25–50 mg promethazine IM during chill episodes.
11. General discomfort: Allow more rest and administer anxiolytics such as diazepam or chlorpromazine as appropriate.
12. All AEs must be followed up until resolution or loss to follow-up. AE resolution is defined as return to baseline health or when the investigator deems no further improvement or deterioration is expected. Follow-up methods may include hospitalization, outpatient visits, home visits, telephone calls, or written communication, depending on severity.

# 11. Statistical Analysis of Study Results

**11.1. Dataset Definitions**

- 1. Full Analysis Set (FAS)

All randomized subjects, regardless of whether they received aerosolized EV treatment are included. Analysis will be conducted according to the Intention-To-Treat (ITT) principle.

- 1. Per-Protocol Set (PPS)

Randomized subjects who received at least one dose of the assigned aerosolized EV treatment and had no major protocol deviations, as well as control subjects who did not receive EV aerosol treatment are included. Criteria for exclusion from the PPS will be defined prior to database lock and will be detailed in the statistical analysis plan.

- 1. Safety Analysis Set (SAS)

Randomized subjects who received at least one dose of aerosolized EVs are included. This set will be used for all safety evaluations. Subjects who were not randomized but received the study treatment will have their safety data listed separately and used only for overall safety evaluation of the study treatment.

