**7.2. Dosage and Administration**

Based on results from animal studies, prior volunteer applications, and relevant literature, the administration method is as follows:

Investigational Product

- Name: Human umbilical cord mesenchymal stem cell-derived extracellular vesicle nebulized solution
- Specification: 2 ml: 2×10⁹ particles
- Storage condition: 2°C–8°C
- Dosage and administration: Inhalation twice daily, 2 ml each time, diluted with 6 ml of normal saline and administered via nebulization at 09:00 ± 30 min in the morning and 20:00 ± 30 min in the evening, for a 7-day treatment course.

Placebo Control

- Name: Normal saline
- Specification: 8 ml
- Storage condition: Store below 25°C, avoid direct sunlight, high temperature, or freezing
- Dosage and administration: Inhalation twice daily, 8 ml each time via nebulization at 09:00 ± 30 min in the morning and 20:00 ± 30 min in the evening, for a 7-day treatment course.

To ensure patient safety, the first 4 subjects will be enrolled sequentially. Each subject will be observed for 24 hours after the initial treatment. If no adverse reactions are noted, the next subject will begin treatment. After all 4 subjects have completed the treatment, a safety assessment will be conducted before full clinical trial rollout.

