**11.5. Safety Analysis**

A detailed listing of all adverse events occurring during the trial will be provided. Changes in laboratory results (normal/abnormal) before and after the trial and their relationship to the study drug will be assessed. The incidence of adverse events in each group will be summarized. Safety analyses will be based on the Safety Analysis Set and conducted by treatment group. Treatment-emergent adverse events (TEAEs) and serious adverse events (SAEs) will be summarized. Descriptive statistics will be used to summarize laboratory findings, symptoms, vital signs, physical examinations, and ultrasound results. Abnormal values will be flagged.

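### The Safety Analysis Set in section 11.1 admits only patients dosed with EVs, which contradicts the by-group safety analysis in section 11.5 and leaves the placebo arm out of the primary (safety) analysis

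*Protocol*

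**What the plan says.** Protocol section 2.1 makes safety the primary objective: "To evaluate the safety of inhaled extracellular vesicle therapy in patients with pulmonary fibrotic lesions". Section 4.1 describes a placebo-controlled design with 1:1 randomization, and section 6 plans 12 patients per arm, 24 in all.

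Section 7.2 describes the control product as "Name: Normal saline", given as "Inhalation twice daily, 8 ml each time via nebulization". It contains no vesicles.

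Section 11.1 sets the membership of the Safety Analysis Set and fixes its scope: "Randomized subjects who received at least one dose of aerosolized EVs are included. This set will be used for all safety evaluations". The same section builds the Per-Protocol Set (PPS) from dosed EV patients without major deviations, and brings in the controls by a separate clause: "as well as control subjects who did not receive EV aerosol treatment are included".

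Section 11.5 states: "Safety analyses will be based on the Safety Analysis Set and conducted by treatment group". It also calls for adverse event incidence to be summarized for each group and for a listing of all adverse events in the trial.

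**The concern.** The membership rule depends on having received the active product, not on having received study treatment. In a placebo-controlled trial this shuts out the control arm by definition, and here it does so for the set on which the primary objective is analysed.

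The placebo arm is the only concurrent comparison for events that nebulization itself, the lung disease or chance could produce. Section 10.6 anticipates discomfort during nebulization and dyspnea afterwards. Saline inhalation or the underlying disease could plausibly cause either. Without a placebo column from the same analysis set, a rate in the EV arm has no concurrent rate beside it. An analyst working from section 11.1 would have no placebo patients to tabulate. One working from section 11.5 would have to go outside the defined set to do so.

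**Working it through.** No sample-size formula or test is involved. The check applies the written rule to the two planned arms and then compares the sections.

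1. **Plan's own figure.** 24 patients at 1:1 gives 24 × 1/2 = 12 per arm, which agrees with section 6.

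2. **Rule applied to each arm, assuming everyone is dosed as assigned.**
   - EV arm: each patient has had at least one EV dose, so 12 of 12 enter.
   - Placebo arm: each patient has had saline only, so 0 of 12 enter.
   - Set as written: 12 + 0 = 12. Excluded: 24 − 12 = 12, and 12/24 = 50% of those randomized.

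3. **Could the EV wording be shorthand for study treatment of either kind?** The PPS definition in the same section speaks against this. There, controls are the subjects who did not get EV aerosol, and they are added by their own clause. The term therefore means the active product, and the authors wrote an extra clause when they wanted controls included. The Safety Analysis Set has no such clause.

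4. **Section 11.1 against section 11.5.**
   - Section 11.1: all safety evaluations use a set that contains no placebo patient dosed as assigned.
   - Section 11.5: safety analyses use that same set, by treatment group, with incidence for each group.
   - A by-group summary needs at least two groups, and the set supplies one. Section 11.5 cannot repair the definition, because it relies on it.

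5. **After the correction.** With membership based on at least one dose of study treatment, EV or placebo, the planned set is 12 + 12 = 24, and the summary required by section 11.5 can be produced.

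**The case against.** The strongest reply is that the protocol plainly intends a two-arm safety summary. Section 11.5 asks for results by group, for incidence in each group and for a full listing of adverse events. Section 11.1 also uses its terms loosely: the Safety Analysis Set paragraph itself moves from EVs to study treatment when it turns to non-randomized subjects. On this view the sentence is a drafting slip that any analyst would read sensibly.

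Much of that stands. A reader might infer that the sponsor means to discard the placebo arm, or that placebo safety data will be lost. The documents support neither. The schedule of assessments and section 10.1 collect adverse events, laboratory results and vital signs without distinction by arm, and placebo events would appear in the listing. Nor is the placebo arm the only reference of any kind: sections 2.1 and 11.5 also look at change from before to after treatment, so baseline is a further, weaker reference. What the reply does not do is make the text workable. The intent shown in section 11.5 conflicts with a definition that the protocol states outright. This is also not a detail left to a statistical analysis plan, because a later plan that admitted placebo patients would depart from the protocol's own definition.

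A reader might also infer that the PPS is biased, because its dosing and deviation conditions are worded for EV patients only. That goes too far. Section 11.1 leaves the PPS exclusion criteria to the statistical analysis plan. Section 5.4 removes subjects of either arm who never received the investigational drug, if that term covers placebo. Section 11.2 bases efficacy on intention to treat, and no analysis in section 11 is assigned to the PPS. The uneven wording is worth tidying, but no bias follows from it.

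**Conclusion.** The point holds as a wrong definition that contradicts another section. As written, the Safety Analysis Set excludes every placebo patient dosed as assigned: 12 of the 24 planned, or 50%. The by-group safety analysis in section 11.5 cannot be carried out on it, and the concurrent control is missing from the analysis of the primary objective. The definition should be corrected before any safety analysis is run.

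The count assumes that all 24 patients are enrolled and dosed as assigned; a control given EVs in error would enter the set. The loss concerns the analysis set and not the collected data. The imprecision of any rate based on 12 patients comes from the sample size, and the correction would not change it.

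**What to change.** In section 11.1, define the Safety Analysis Set as all randomized subjects who received at least one dose of study treatment (EV or placebo), analysed by treatment actually received. Section 11.5 can then stand unchanged.

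As a minor alignment in the same section, state the base PPS criteria identically for both arms: at least one dose of the assigned study treatment and no major protocol deviation.

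The cost is two sentences in one section. No additional data, visits or patients are needed.

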**9.2. Safety Assessment**

Both short-term and long-term safety assessments are included. All adverse events (AEs), including serious adverse events (SAEs), should be monitored and recorded. Detailed records should be maintained for vital signs, clinical symptoms and signs, routine blood tests, urinalysis with pregnancy test, infectious disease screening, blood biochemistry, electrocardiogram (ECG), peripheral oxygen saturation, tumor markers, IL-6, IL-10 levels, immune cell function, and lymphocyte subsets.

1. Short-term (In-Hospital) Safety Monitoring

- Physical examination: including BMI, heart rate, blood pressure, respiratory rate, fingertip oxygen saturation, and complete physical examination.
- Blood tests: including complete blood count (CBC), urinalysis with pregnancy test, infectious disease screening, blood biochemistry, tumor markers, and IL-6, IL-10 levels.
- Auxiliary tests: including ECG and chest HRCT.
- Monitor and record any adverse events during administration of the investigational product. If adverse events occur, follow up with the patient until resolution or end of treatment.

1. Long-term Safety Evaluation

Long-term safety will be evaluated by monitoring the occurrence of adverse events (AEs) or serious adverse events (SAEs) at 6 and 12 months after treatment with extracellular vesicles.

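### The Safety Analysis Set requires a dose of EVs, so no placebo patient enters it and the primary safety objective has no control group

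*Protocol*

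**What the plan says.** Section 11.1 of the protocol sets both the entry rule and the scope of the Safety Analysis Set: "Randomized subjects who received at least one dose of aerosolized EVs are included. This set will be used for all safety evaluations".

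The control treatment is in section 7.2, where the placebo entry reads "Name: Normal saline" and the administration is "Inhalation twice daily, 8 ml each time via nebulization". It contains no vesicles.

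Section 11.5 gives the layout of the analysis: "Safety analyses will be based on the Safety Analysis Set and conducted by treatment group". It also calls for adverse event incidence to be summarized for each group.

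Two other places bear on the point. Section 10.3 takes all participants as the denominator for adverse reaction rates. Section 9.2 describes long-term safety as events "at 6 and 12 months after treatment with extracellular vesicles".

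**The concern.** Section 2.1 makes safety the primary objective, and section 4.1 describes a 1:1 randomized, placebo-controlled design. The saline arm is there so that what happens on EVs can be set against what happens to similar patients who nebulize the same volume without EVs. If the safety population admits only EV recipients, that comparison is gone from the primary analysis.

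This matters in these patients. Section 10.6 lists dyspnea, nausea and discomfort during nebulization among the possible adverse events. Such events could also come from the lung disease or from inhaling 8 ml of fluid twice a day. A description of the EV arm alone gives no concurrent rate against which to judge them.

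The plan also leaves open which population and which denominator the analyst should use. Sections 11.1, 11.5 and 10.3 point in different directions, and a choice left open can end up being made after the data are seen.

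**Working it through.** The protocol gives no power calculation or event rate to reproduce. The check is a count of who qualifies, followed by a reading of the wording.

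**Inputs**
- 24 patients, 12 per arm (section 6), which agrees with 1:1 allocation (section 4.1).
- Entry rule: randomized, and at least one dose of aerosolized EVs (section 11.1).
- Control treatment: nebulized normal saline (section 7.2).

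**Membership, assuming no dosing errors**

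| Rule | EV arm | Placebo arm | Total |
| --- | --- | --- | --- |
| Section 11.1 as written | up to 12 | 0 | at most 12 of 24 (12/24 = 50%) |
| At least one dose of EV or placebo | up to 12 | up to 12 | up to 24 of 24 |

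**Can the EV wording be read as shorthand for study treatment?** Section 11.1 itself argues against it.
1. The Per-Protocol Set, defined just above, adds the controls by a separate clause: "as well as control subjects who did not receive EV aerosol treatment are included". In this section, EV aerosol is something that controls do not receive.
2. The Safety Analysis Set has no such clause for controls.
3. Later in the same definition, on subjects treated without randomization, the text uses the broader term study treatment. The term was available but was not used in the entry rule.

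**Does section 11.5 repair it?** No. It asks for results by group but takes the Safety Analysis Set as its population. Under the section 11.1 rule that set has one group.

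**Denominator.** Suppose 3 related events are counted (an assumed number). On the set as written the rate is 3/12 = 25.0%. With all participants as denominator, as in section 10.3, it is 3/24 = 12.5%. The same data give a twofold difference, and neither figure is a by-group comparison.

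**What one arm can show (assumed counts)**
- 0/12 events on EVs: the one-sided upper 95% bound is 1 − 0.05^(1/12) = 22.1%. The two-sided exact upper bound is 1 − 0.025^(1/12) = 26.5%.
- 4/12 on EVs: 33%, exact (Clopper-Pearson) 95% CI 9.9% to 65.1%. There is no control rate to set beside it.
- If 3/12 occurred on saline (25%, 5.5% to 57.2%), the difference would be 33.3 − 25.0 = 8.3 percentage points. Its Newcombe 95% interval is about −26 to +40 points.
- With a saline arm at 0/12, Fisher's exact two-sided p is 0.093 for 4/12 on EVs and 0.037 for 5/12. The protocol specifies no between-group safety test. These values show only that a marked imbalance could be seen with both arms in the set, whereas no comparison exists with one.

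**The case against.** The strongest reply is that the sponsor plainly meant to include placebo. Section 11.5 asks for results by group and for a listing of every adverse event in the trial. On this view two sections conflict and the second shows the intent. That is a fair reading of intent, and the wording is probably a drafting slip. It does not settle the matter, because section 11.5 names the faulty set as its population.

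A second reply is that no data are lost, and this stands. Section 10.1 collects adverse events from consent to study completion, and Table 1 schedules safety assessments without restriction by arm. The loss is in the summarized analysis, not in collection.

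Third, the wording in section 9.2 may be only a time anchor. This also stands. Section 4.3.2, Table 1 and section 12.1 plan the later contacts without restriction by arm, so placebo patients are not dropped from long-term follow-up. Section 9.2 is a matter of tidying.

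Fourth, with 12 per arm the placebo group separates causes only weakly. That is true: the interval of about −26 to +40 points comes from the sample size and would remain after the correction. A weak control is still what the design provides, and removing it leaves no contrast at all.

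**Conclusion.** The concern holds. As written, 0 of 12 placebo patients belong to the population used for all safety evaluations. At most 12 of the 24 randomized patients contribute to the primary objective, and the by-group safety summaries of section 11.5 cannot be produced. The count rests only on the stated sample size and on correct dosing. The event counts used for illustration are assumptions, and the conclusion does not depend on them.

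This must be corrected even though it is probably a drafting error, because it governs the analysis of the primary objective. A statistical analysis plan was not available and may define the set differently. The protocol, however, has not left the definition open; it has stated it wrongly.

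**What to change.** In section 11.1, redefine the Safety Analysis Set as all randomized subjects who received at least one dose of study treatment, whether EV solution or saline placebo, analysed by the treatment actually received. The last part also settles where a patient given the wrong product is counted.

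Align the related text:
- **Section 10.3:** make the denominator for adverse reaction rates the number of subjects in the Safety Analysis Set in each group.
- **Section 11.5:** no change of substance is needed, since its by-group summaries become possible once the set is corrected.
- **Section 9.2:** refer to 6 and 12 months after study treatment, in both groups. This is editorial.

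The cost is a few sentences of protocol wording, with no additional patients, visits or data. The change should be made before any unblinded safety data are reviewed, so that the population and denominator are not chosen with results in hand.
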